## Discussion

Several studies showed that both Alfredson isolated eccentric and Silbernagel combined concentric-eccentric training are beneficial in terms of symptom reduction in midportion AT. [14, 16, 17, 25, 26] However, whether any of these programs is more effective has yet to be determined. This study protocol describes the first RCT directly comparing the effectiveness of both programs. We designed a pragmatic study, in which we try to replicate how both programs are described in the clinical setting. By using the VISA-A – a condition-specific validated questionnaire that is widely recommended for use in research and clinical practice – as the primary outcome measure, we hope that comparison of our results to other studies and clinical practice will be enabled.

Besides the effectiveness on symptom reduction and QOL, our study also compares the effectiveness of both programs on functional performance of the muscle-tendon unit. This comparison has not previously been performed, whilst research has shown that functional deficits of the muscle-tendon unit may still persist after 1 year in patients with AT, even though symptoms have fully recovered. [45].

We will also assess differences in cost-effectiveness in the mid-term and long term. Cost-effectiveness may be an important parameter for clinical decision making, but to date, research investigating cost-effectiveness in AT treatment is scarce. [17] We expect no difference in direct intervention-related costs, since both programs are performed at home and the amount of supervising physiotherapy sessions is similar, but we are predominantly interested in potential differences in indirect costs (e.g. absenteeism of work, school and sports) between both programs.

Recruitment for this trial will be performed in different institutions, i.e. sports medicine clinics, hospitals, and general practices. Therefore, participant characteristics may differ, and this potentially could lead to different subgroups of participants. No stratified randomization for referral type is performed, but by including recreational athletes, it is expected that both study arms will consist of relatively homogeneous groups. Furthermore, we try to collect important participant characteristics that may cause potential bias to the results of this study. Nonetheless, it should be acknowledged that the participants’ metabolic health is not fully covered, whilst research showed that this may be a confounding factor. [46].

We feel that the pragmatic nature of our study is a strength, as it mimics the clinical setting. Nevertheless, a potential limitation of this pragmatic design that we cannot draw any conclusions on the underlying mechanism of possible differences in effectiveness, since we have not controlled for many of the potential contributing factors.

Additionally, our study does not include a study arm performing no exercise intervention. Therefore, it remains unknown whether potential improvements are caused by the exercise programs or by the natural course of the condition. Although it is generally agreed that exercise therapy is crucial in the treatment of AT, [3, 9, 12] we acknowledge that the lack of a non-exercise (wait-and-see) group is a potential limitation of the study design.

In summary, this multicenter two-arm RCT will compare the effectiveness of the Alfredson isolated eccentric to the Silbernagel combined concentric-eccentric program for treatment of chronic midportion AT. The results of this study will enlarge the evidence base on different exercise programs for AT, and may aid the clinician in choosing the most appropriate program for their patients.

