### Sample size calculation

Sample size was calculated based on two high quality RCTs having investigated the Alfredson program and the Silbernagel program respectively, and using the VISA-A questionnaire as their primary outcome measure. [16, 26] We used the respective change (mean ± standard deviation [SD]) in VISA-A scores for the groups that followed the above-mentioned exercise programs:Rompe et al. [16] (*n* = 25): VISA-A Δ 22.4 ± 19 for the Alfredson programSilbernagel et al. [26] (*n* = 19): VISA-A Δ 34 ± 17 for the Silbernagel program

This resulted in an expected effect size of 0.64 between both exercise programs, with an expected VISA-A change score that exceeds the minimal clinically important difference of 10 points. [23] Using G*Power 3.1, and assuming α two-sided = 0.05 and a power of 0.80, a total of 39 participants in each study arm was required. The dropout rate in the above-mentioned studies was 4% [26] and 9% [16] respectively. We chose to take the most conservative dropout rate of 9% into account, resulting in a required amount of 86 in total, i.e. 43 participants in each arm.

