### Outcome measures

#### Baseline assessment

During baseline assessment – besides the primary, secondary and other outcome measures – demographic and anthropometric characteristics such as age, weight, height, body mass index, job type and activity level, sport type and activity level, and referral type are recorded using a standardized questionnaire. Additionally, waist circumference will be recorded with a flexible tape measure, [32] range of motion for ankle dorsiflexion will be recorded using the weight bearing lunge test, [33] and dorsiflexion range of motion of the first metatarsophalangeal joint will be measured with a standard goniometer. [34] Body weight and sport activity level will also be recorded at T1, T2 and T3, as these variables are thought to vary throughout the study period and thus may potentially influence the study outcome.

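### Restricting entry to recreational athletes does not balance referral type between arms, and the stated comparison names no adjustment for it: a small loss of precision that a recorded covariate could recover

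*Protocol article*

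**What the plan says.** The Discussion of the protocol article notes that patients will come from sports medicine clinics, hospitals and general practices, and that as a result "participant characteristics may differ, and this potentially could lead to different subgroups of participants". The next sentence reads "No stratified randomization for referral type is performed, but by including recreational athletes, it is expected that both study arms" will be fairly homogeneous. The authors add that they collect characteristics that might bias the results.

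Under Baseline assessment, "sport type and activity level, and referral type are recorded using a standardized questionnaire"; Table 2 lists the same item at baseline. The descriptions of randomization, under Study design and setting and under Randomization procedure, name no stratification factor.

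Statistical analyses compares the programs by ANOVA and names no covariate. It gives baseline data two other uses: tests of baseline comparability, and a regression that models the prognostic value of baseline variables.

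**The concern.** The subgroups that the authors foresee are subgroups among recreational athletes, because sports participation is required of everyone, whatever the route of referral (Participant selection). A criterion met by all participants cannot even out the mix of referral types between two arms of 43. Nothing else in the stated design does so, and the stated between-program analysis does not say that it allows for referral type.

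If referral type predicts VISA-A change, two linked things follow. A chance imbalance shifts the observed program difference in this one trial, and the variance between referral types stays in the error term. Both can be reduced with a variable that is already collected. Neither baseline tests nor a separate prognostic regression does this for the program comparison.

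**Working it through.** **Inputs from Sample size calculation.** Alfredson change 22.4, SD 19. For the other arm, "VISA-A Δ 34 ± 17 for the Silbernagel program". Design: "assuming α two-sided = 0.05 and a power of 0.80". Result: "a total of 39 participants in each study arm was required". Dropout is 9%, giving 43 per arm and 86 in total.

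**Assumed, because the document gives no figure.** Share of participants with a given referral type: 20%, 30% or 50%. Gap in mean VISA-A change between referral types: 5, 10 or 15 points.

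**1. The plan's own figure.** SD = √((19² + 17²)/2) = 18.03. Effect size = (34 − 22.4)/18.03 = 11.6/18.03 = 0.643, which agrees with the stated 0.64. The noncentral t calculation with 0.643 needs 38.9, so 39 per arm; 39/0.91 = 42.9, so 43 per arm and 86 in total. The plan's figures reproduce. Power at 39 per arm is 80.1% (79.7% if the effect size is first rounded to 0.64).

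**2. Chance imbalance.** Let K of the 86 participants have the referral type. With 43 allocated to each arm, the number in one arm is hypergeometric(86, K, 43).

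| Prevalence (K) | SD of difference in share | P(≥10 points) | P(≥15 points) | P(≥20 points) |
|---|---|---|---|---|
| 20% (17) | 8.6 points | 28% | 10% | 2.8% |
| 30% (26) | 10.0 points | 24% | 10% | 3.4% |
| 50% (43) | 10.8 points | 39% | 20% | 8.4% |

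Points here are percentage points. The 10-point column dips at 30% because counts are discrete: with K even, the difference in counts is even, so the smallest one that qualifies is 6 of 43, against 5 of 43 when K is odd.

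**3. Shift in the program difference.** Shift = gap × imbalance. With a 10-point gap and a 15-percentage-point imbalance, 10 × 0.15 = 1.5 VISA-A points. The planned difference is 11.6 points, so this is 13% of it. The standard error is 18.03 × √(2/39) = 4.1 points, so the shift is about 0.37 standard errors.

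**4. Gain from adjustment.** Variance explained: R² = p(1 − p) × gap²/18.03². The residual SD is 18.03 × √(1 − R²). Power is from the noncentral t at 39 per arm, starting from 80.1% unadjusted.

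| Assumed gap | R² at p = 20% | R² at p = 50% | Adjusted power |
|---|---|---|---|
| 5 points | 1.2% | 1.9% | 80.6–80.8% |
| 10 points | 4.9% | 7.7% | 82.0–83.1% |
| 15 points | 11.1% | 17.3% | 84.5–87.0% |

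For example, at p = 50% and a gap of 10, R² = 0.25 × 100/325 = 7.7%.

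**5. Cost.** If referral type explains nothing, giving up two degrees of freedom (76 to 74) lowers power from 80.10% to 80.08%, which is less than 0.1 point.

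**The case against.** The strongest reply is that nothing here is invalid. Randomization balances referral type in expectation, the unadjusted comparison is unbiased with valid type I error, and its standard error already reflects chance imbalance. The shift in one trial and the leftover error variance are therefore one loss seen from two sides and should not be counted twice. All of this stands. Leaving referral type unstratified in a trial of 86 is an acceptable choice, and the authors disclose it.

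A reader might infer more than the text supports, in three ways:

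- *That the protocol claims its entry criterion balances referral type.* It does not. It expects fairly homogeneous arms, and restricting entry can narrow the spread of participants. The argument is weak, not empty.
- *That the protocol expects outcome to differ by referral source.* It says only that characteristics may differ and that subgroups could result. It states no difference in VISA-A.
- *That referral type will go unused.* The article names no covariate, but a condensed article may leave the covariate list to a fuller document that is not shown, and referral type could enter the prognostic regression. The supportable statement is that the stated comparison names no adjustment for it.

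The size also depends on the assumptions. A prevalence of 50% gives the largest imbalance probabilities of those tried. A 10-point gap equals the minimal clinically important difference cited in the article, and a 15-point gap exceeds the planned treatment difference.

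This leaves the point minor but does not remove it. The homogeneity sentence is the published reason for accepting no stratification, and it does not answer the possibility raised in the sentence before it.

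**Conclusion.** The point holds in a limited form. The entry criterion does not balance referral type between arms, and the stated ANOVA names no adjustment for a variable that the trial records. The consequence is possible loss of precision and possible chance imbalance. It is not bias, and it is not an error in the sample size, which reproduces.

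An imbalance of at least 10 percentage points has probability 24% to 39%, and one of at least 15 points 10% to 20%, at assumed prevalences of 20% to 50%. Adjustment adds less than 1 point of power for an assumed 5-point gap, about 2 to 3 points for a 10-point gap and about 4 to 7 points for a 15-point gap. If referral type is not prognostic it adds nothing, and the document gives no evidence either way. The figures also take the SD of VISA-A change from the sample size section as the error SD of the comparison. This is a minor improvement to the plan, worth making because it costs almost nothing.

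**What to change.** Drop homogeneity among recreational athletes as the reason for not stratifying. Say plainly that allocation is not stratified by referral type and that the analysis will allow for it. Then add one line to Statistical analyses, for example: *Referral type (sports medicine, hospital, general practice) is a prespecified covariate in the between-program comparison of 12-month VISA-A; sparse categories will be merged before unblinding.* Report referral type by arm as description only.

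The variable is already collected, and the article says the randomization code stays closed until the analysis is complete, so the rule can be fixed without knowledge of allocation. The cost is one or two degrees of freedom, less than 0.1 point of power. If an unshown analysis plan already lists this covariate, only the Discussion sentence needs to change.

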### Trial status

Enrollment of participants has started since November 2016. On July 3 2017, 14 participants have been included.

## Abbreviations

ANOVA: analysis of variance
AT: Achilles tendinopathy
CMJ: countermovement jump
EQ-5D: Euroqol instrument
GPE: global perceived effect
HSRT: heavy slow resistance training
ITT: intention-to-treat
QOL: quality of life
RCT: randomized controlled trial
SF-12: 12-item short form health survey
UMCU: University Medical Center Utrecht
VAS: visual analog scale
VISA-A: Victorian Institute of Sports Assessment – Achilles
